#### Sociodemographic variables

These include age, ethnicity, gender identity, sex, employment status, education level, and annual household income.

### Other variables that may affect the outcome

#### Closeness to the offender

The measurement will employ the Inclusions of Others in the Self scale (IOS) [50], comprising seven pairs of circles with varying degrees of overlap (1, no overlap, to 7, maximal overlap) describing the relationship between oneself and the other. Participants will indicate their relationship with the one who caused them harm by selecting the pair of circles that best reflects their relationship. The assessment will be conducted at T1 with the Love thy Enemy task.

#### Experiences of the app-based exercises

Participant will be asked to provide feedback on their meditation experiences. This assessment will involve completing questionnaire containing Likert-scale items and open-text questions at T2 & T3.

#### Frequency of the meditation or mindfulness practices after the end of the intervention

Participants will complete a self-report assessment regarding the frequency of their practices following the completion of the 8-week intervention.

### Qualitative measure

Participants will be provided with a notebook and instructed to keep a diary for reflective purposes. The diary will serve to evaluate any potential adverse events associated with the meditation practices, as well as to explore the effects of the practice on participants’ daily life. Furthermore, participants will be prompted to provide feedback on their daily meditative experiences within the app following each session. This prompt aims to evaluate their experiences during meditation practices, focusing primarily on mood, emotions, and the effectiveness of the session. These measures will be assessed throughout the 8-week intervention.

## Adverse events and safety monitor

We have established an expert panel to guide the study’s design and intervention. Additionally, a dedicated study coordinator oversees the logistical and operational aspects of our research. Given that the potential for adverse events linked to meditation practices [67], we will assess this risk by including a self-report measure for adverse events. Participants will be also asked to reflect on their experiences during the practices. To address concerns, participants can consult religious experts from our advisory board regarding any potential adverse effects of the interventions. They will also be encouraged to promptly contact the lead researcher if adverse events occur, as outlined in the participant information sheet.

Participants undergoing the cold pressor task procedures may experience discomfort or pain, inherent to the procedure’s design. They will be informed that they have the option to discontinue the procedure and remove their hand from the cold water at any time. The cold pressor task is a well-established procedure, and unexpected adverse effects related to the cold pressor task procedure are unlikely to occur. Therefore, based on our risk assessment and the low anticipated risk, a formal data monitoring committee and modifications of allocated intervention are considered unnecessary for this study. It is also unlikely that participants will require post-trial care. However, the lead researcher will closely monitor and document any potential adverse events. Participants will be informed of their right to withdraw from the trial at any time without needing to provide a reason.

### Analysis plan

#### Quantitative data

The analyses will follow both intention-to-treat principle and per-protocol principle, requiring a minimum completion of four days of meditation sessions per week over the 8-week intervention period and complete all required assessments. This study will consider a result with a p-value lower than 0.05 as statistically significant. A series of mixed-design Repeated Measures Multivariate Analysis of Variance (RM-MANOVA) will be used to test the mean difference in the outcomes among conditions (Spiritual meditation, mindfulness, and waitlist control groups) across T1, T2 and T3 as well as within participants across all time points (T1, T2 and T3). The specific prosociality variable, measured by Charitable Giving task, will be only compared between groups at T2. When justifiable, missing data will be imputed using multiple imputation of chained equations [68]. 

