## Research question and hypotheses

This study addresses the effects of heart-centred meditation from the Christian and Islamic traditions, compared to secular practices, on social functioning, physiology, cognition, and mental health. The key question is whether the regular practice of Christian or Islamic heart-centred contemplation fosters positive outcomes at the interpersonal and the individual levels, as compared to a standardised mindfulness-based stress reduction intervention (MBSR) and a waitlist control condition.

To address these questions, this study will develop (a) an 8-week intervention based on heart-centered Christian and Islamic contemplative practices; (b) a stratified 3-arm randomised controlled trial (RCT) with contemplations (Christian and Islamic), an active control (MBSR) and a waitlist control. The contemplation and MBSR programs will be delivered through a mobile app.

We hypothesise that when compared to baseline, individuals undertaking the heart-centred contemplative practices will show: (1) greater prosociality, forgiveness, empathy, and perspective taking; (2) increased pain tolerance and attention, and reduced subjective ratings of pain intensity, reduced stress reactivity as measured by HR and HRV, and reduced psychophysiological reactivity associated with forgiveness as measured by HR and HRV; (3) reduced self-reported stress, depression, anxiety; (4) increased subjective wellbeing and positive affect as well as reduced negative affect. We also hypothesise that these outcomes will be greater for participants in the heart-centred contemplations compared to those in the waitlist control condition. We have no specific predictions for comparing the outcome of the religious (Christian or Islamic) *versus* MBSR interventions.

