### Methods

#### Trial design

The study employs the Standard Protocol Items Recommendations for Interventional Trials (SPIRIT) [40] as the reporting guideline for this protocol and adheres to Consolidated Standards of Reporting Trials (CONSORT) [41] to ensure quality in study planning, implementation, and reporting.

Figure 1 and Table 1 show the study procedure and the setup of the randomised control trial. This is a 3-arm stratified randomised controlled trial, with four groups distributed across two variants of the spiritual meditation condition (Christian and Islamic), MBSR, and a waitlist control condition. Participants will be first stratified into Christian and Muslim samples and then randomly allocated to one of the three conditions. Individuals assigned to the spiritual meditation condition will be further stratified into either a Christian or an Islamic contemplation subgroup within the spiritual meditation condition based on their religious affiliations.

Participants in the spiritual meditation groups and the secular mindfulness group will receive 8-week interventions, commencing with an initial face-to-face meeting, where they will practice the first session of the guided meditation course using the mobile app. Following that, they will continue with daily guided practices lasting approximately 20 min through the app. Assessment will be held at three time points including pre-intervention (T1, baseline), after the 8-week intervention (T2), and three months after the intervention (T3). Participants in the waitlist control group will only attend the assessments at T1 and T2, as due to ethical reasons they will be given the option to start using the Christian or Islamic meditation App after testing at T2.

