## Recruitment, screening, and enrolment

The recruitment process started on 22 July 2024. Non-clinical samples of Christian and Islamic healthy adult participants will be recruited and enrolled from the local institutions through their internal participant pools, online adverts, distributing flyers, and collaboration with religious communities.

Potential participants will be contacted via email with detailed information in a written form and will be required to fill out a pre-screening online questionnaire. Their self-reports will be assessed through inclusion and exclusion criteria to determine their eligibility. The reason for ineligibility will be retained in accordance with CONSORT standards [41]. 

Eligible participants will receive information about the study including its objective and procedures. Subsequently, research team member will ask participants to provide informed consent for study enrolment. All enrolled participants will be invited to take part in the baseline assessment (T1) and the follow-up assessment (T2) with measures of social functioning, physiology, and cognition. A set of online measures concerning mental health, religiosity, socioeconomic status, demographics, social value orientation, and meditation social desirability will be taken at home before T1. Additionally, participants in the religious contemplation groups and MBSR will attend an online 3-month follow up assessment. All participants will be compensated with an INR 2,000 as compensation for their time.

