### Intervention content

All interventions will be delivered through an 8-week program of daily audio-guided meditations of approximately 20-minutes. There will be a total of eight different meditations per condition, one per week, where each meditation is repeated across seven days. To ensure participant engagement in the meditation practice, the app will unlock the next session for the participant only after completing the preceding day’s session. Similarly, progression to the next week’s meditation session requires completing at least four sessions in the preceding week. The app will track participants’ completion of practice sessions and record daily responses to two brief questions about mood and meditation experience. Participants can maintain their daily religious practices during the 8-week program.

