### Waitlist condition

Participants assigned to the waitlist control condition will take part in the assessments at T1 and T2 but will not participate in any of the interventions. They will be given access to either the Christian or Islamic spiritual meditation app version after they complete the assessment at T2.

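### The per-protocol rule cannot be applied evenly to a waitlist with no sessions and no T3, so its active-versus-waitlist contrast is not a randomised comparison, and the protocol does not rank it below intention-to-treat

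*Protocol article*

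**What the plan says.** The Quantitative data section of the analysis plan states "The analyses will follow both intention-to-treat principle and per-protocol principle". The same sentence gives the per-protocol condition: "requiring a minimum completion of four days of meditation sessions per week over the 8-week intervention period and complete all required assessments". One significance threshold of 0.05 follows. The section does not say which analysis carries the conclusion. It compares all three conditions: spiritual meditation, mindfulness and waitlist.

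The arms do not share the features on which the rule depends.

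- **Sessions.** Under Waitlist condition, these participants "will take part in the assessments at T1 and T2 but will not participate in any of the interventions". App access comes only after T2.
- **Assessments.** Under Trial design, "Participants in the waitlist control group will only attend the assessments at T1 and T2". Under Recruitment, screening, and enrolment, "participants in the religious contemplation groups and MBSR will attend an online 3-month follow up assessment".
- **App gate.** Under Intervention content, moving to the next week's meditation "requires completing at least four sessions in the preceding week", the same threshold as the per-protocol rule.

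The protocol's only directional between-group hypothesis, under Research question and hypotheses, is that "these outcomes will be greater for participants in the heart-centred contemplations compared to those in the waitlist control condition". No prediction is made against MBSR.

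**The concern.** A per-protocol set is chosen on behaviour after randomisation. That is a known weakness in any trial, but here the choosing is also lopsided by construction. Active participants must keep up a practice for eight weeks to stay in the set, while waitlist participants have nothing to keep up. The lopsidedness falls on the contrast that the directional hypothesis concerns.

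The assessment clause adds a second problem. If required assessments include T3, an active participant with complete T1 and T2 data can be dropped from a T2 comparison for missing a visit three months later. No waitlist participant can be dropped for that reason.

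If persistence goes with how people would have changed anyway, the per-protocol contrast shows a difference with no treatment effect. Because the two analyses are unranked, such a difference could be reported as a main result of the trial.

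**Working it through.** **1. The rule applied arm by arm**

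| Criterion | Spiritual | MBSR | Waitlist |
|---|---|---|---|
| Four session days a week for 8 weeks | can exclude | can exclude | no sessions: excludes all, or does not apply |
| T1 and T2 complete | can exclude | can exclude | can exclude |
| T3 complete, if counted as required | can exclude | can exclude | does not apply |

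Read literally, the rule leaves no per-protocol waitlist. Read charitably, the first and third rows act on the active arms only. The two active columns are identical, so spiritual versus MBSR does not share the defect, although adherence may still differ between those arms.

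**2. Outcomes touched by a T3 condition**

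Table 2 lists six primary measures. The Dictator Game, social value orientation, Charitable Giving, forgiveness and empathy are not measured at T3. Only perspective taking is. A T3 condition is therefore irrelevant to five of the six.

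**3. The plan's own sample size, used for the group sizes**

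The Power analysis section gives 288 in total, 72 in each of four groups, after 10% dropout. For the within-between interaction of a repeated-measures ANOVA, λ = f²·N·m/(1−ρ), with k = 4 groups, m = 3 time points, alpha 0.05, power 0.85, f = 0.1 and ρ = 0.5 (ρ is assumed). This gives N = 260. Then 260/0.9 = 289, or 260 × 1.1 = 286, which bracket 288. The figure reproduces only if the printed 0.1 is f, not f². That is a separate notation matter and does not affect this point. The check below uses 144 spiritual (two groups of 72) and 72 waitlist participants before filtering.

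**4. Size of the selection effect when the true effect is zero**

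Inputs not in the documents, so assumed:
- share of active participants kept, p_a: 40% to 70%;
- share of waitlist kept, p_w: 90%, mirroring the planned 10% dropout and selected on the same propensity;
- correlation r between adherence propensity and outcome change without treatment: 0.2 to 0.3.

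With bivariate normal variables and the top share p kept, the mean propensity of those kept is φ(c)/p, where c is the cut-off:
- p = 0.9: 0.195
- p = 0.7: 0.497
- p = 0.5: 0.798
- p = 0.4: 0.966

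Bias in SD of change = r × [φ(c_a)/p_a − φ(c_w)/p_w].

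The false-positive rate is that of a two-sided z test at 0.05 with SE = √(1/(144·p_a) + 1/(72·p_w)). The slight loss of variance from selection is ignored.

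| r | p_a | Bias (SD) | SE | False-positive rate |
|---|---|---|---|---|
| 0.2 | 0.7 | 0.2 × (0.497 − 0.195) = 0.06 | 0.159 | 6.7% |
| 0.2 | 0.5 | 0.12 | 0.171 | 10.8% |
| 0.2 | 0.4 | 0.2 × (0.966 − 0.195) = 0.15 | 0.181 | 13.6% |
| 0.3 | 0.7 | 0.09 | 0.159 | 8.8% |
| 0.3 | 0.5 | 0.18 | 0.171 | 18.4% |
| 0.3 | 0.4 | 0.23 | 0.181 | 24.8% |

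At r = 0 the bias is zero and the rate is 5%. At r = −0.1 the bias is −0.03 to −0.08 SD, against meditation. If 90% of the active arm is also kept, the bias is zero at any r.

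**5. Which outcome is most exposed**

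Charitable Giving is compared at T2 only and has no baseline. For it, r is the correlation with the level of giving, so a stable trait linked to persistence enters the contrast directly. For the other primary measures a constant trait difference cancels in the condition-by-time contrast, and r must be a correlation with change.

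**The case against.** **A ranking may exist elsewhere.** This is a condensed article, and a fuller plan could make intention-to-treat primary. A reader might infer that the two analyses have equal standing. The text says only that both will be done. That stands, and the missing ranking alone would be a weak point. It does not answer the main one: the rule is stated, and as stated it cannot treat the arms alike.

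**The waitlist is not unfiltered.** A reader might infer that it is. The completeness clause still binds it at T1 and T2, so the asymmetry lies in adherence and T3 only.

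**The direction is not established.** A reader might conclude that the contrast is tilted in favour of meditation. That is plausible if persistent people would have improved more anyway, but nothing in the documents fixes the sign. Agreeableness or conscientiousness, the obvious candidates, are stable traits and largely cancel wherever there is a baseline.

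**Larger figures are easy to produce and hard to defend.** With an assumed independent weekly success of 0.90, 0.90^8 = 43% of active participants qualify. With r = 0.2 and a waitlist kept whole, the bias is 0.2 × 0.9135 = 0.183 SD. If 90% of the waitlist is kept on the same propensity, it falls to 0.2 × (0.9135 − 0.195) = 0.144 SD. Independence between weeks is also unrealistic, since adherence clusters within people and the app gates each week on the one before. With an assumed exchangeable latent correlation of 0.5 or 0.7 and the same weekly success, 63% or 71% qualify.

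**Required may mean required for the outcome analysed.** That reading is open and would remove the T3 problem. The text does not choose it. For perspective taking at T3, requiring T3 is not out of place.

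**Imputation does not settle it.** The plan says "When justifiable, missing data will be imputed using multiple imputation of chained equations", without tying this to an analysis set. Imputing outcomes does not restore participants whom the adherence rule has excluded.

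**Conclusion.** The point holds in a limited form. The per-protocol rule either empties the waitlist or filters the active arms alone on adherence and, on one reading, on T3. On either reading the protocol has no per-protocol active-versus-waitlist contrast protected by randomisation, and it does not say that intention-to-treat decides. That much follows from the text without any assumption.

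The size does rest on assumptions. With 40% to 70% of active and 90% of waitlist participants kept and r between 0.2 and 0.3, the spurious spiritual-waitlist difference is about 0.06 to 0.23 SD, and the false-positive rate is about 7% to 25%. It vanishes at r = 0 and changes sign if r is negative. The documents support neither a claim that the trial is biased towards meditation nor any single figure. The intention-to-treat comparison is planned and is untouched by this filter.

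**What to change.** In the Quantitative data section:

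1. State that conclusions rest on the intention-to-treat analysis of all randomised participants as allocated. Per-protocol is supportive only, and its waitlist contrast is labelled non-randomised.
2. Define per-protocol membership for the waitlist as completion of T1 and T2.
3. Say which assessments are required for which outcome, and do not require T3 attendance for outcomes compared at T2.

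If the effect in adherent participants is of interest, a complier-average estimate from the app's session records against the waitlist is an option. It must state its exclusion assumption, namely that allocation acts only through reaching the session threshold. Practice below the threshold and the lack of blinding both strain that assumption, so it is no substitute for the steps above.

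The cost is a few sentences and no new data. Recruitment began on 22 July 2024, so the wording should be settled before outcome data are analysed. The downside is that a favourable per-protocol result could no longer stand as a main conclusion of the trial.

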## Participants

### Power analysis

This study will recruit non-clinical samples of 144 Christian and 144 Islamic healthy adult participants. An a priori power analysis was conducted using the G*Power software (V.3.1) [42], considering four groups with mixed method repeated measures at three timepoints. The calculation was conducted based on a small effect size of *f*^*2*^ = 0.1, with an alpha value of 0.05, a desired power of β = 0.85. Effect size was set at 0.1 using a conservative approach due to the novel nature of the study to examine the effects of Christian and Islamic contemplation. Calculation was applied to determine the total sample size of 288 participants with (*n* = 72) per group, after adjusting for an estimated dropout rate of 10%.

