### Primary outcomes

The study is primarily assessing changes in interpersonal functioning, measured through prosociality, forgiveness, empathy, and perspective taking. Prosociality will be assessed at T1 and T2 via the *Dictator Game* (DG) [45], *Social Value Orientation* (SVO) [46], and *Charitable Giving* (at T2 only). Empathy and forgiveness variables will be collected via the task *Love thy Enemy* (adapted from Witvliet et al. [47]) at both T1 and T2. Perspective taking will be obtained online at T1, T2, and T3.

Dictator Game (DG) [45]: This computer-based task allocates ten game points to participants and asks them to decide how many of these points they would like to transfer to an anonymous participant. The outcome measure is the number of game points participants are willing to allocate to the anonymous individual. The game points retained by participants will have no influence on their real-life earnings or their compensation fee for taking part in the experiment. Prior studies have shown that individuals engage in prosocial activities irrespective of monetary incentives [48, 49]. 

Social Value Orientation (SVO) [46]: This online task consists of six items with which participants are asked to assign game points for themselves and an anonymous other. Participants will make their allocations by adjusting a slider to indicate their most preferred joint distribution between themselves and the other. A continuous social value orientation score will be computed from these six items based on participants’ choices. The outcome measure will be a single overall SVO score. A higher SVO score represents a higher prosocial preference. The game points kept by the participants will not affect their real-life earnings or their compensation fee for taking part in the experiment.

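### Six unranked primary measures are judged at a flat p < 0.05, with no contrast designated primary and no multiplicity control

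*Protocol article*

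**What the plan says.** Under Primary outcomes, the protocol article states: "The study is primarily assessing changes in interpersonal functioning, measured through prosociality, forgiveness, empathy, and perspective taking". That section and Table 2 break the four constructs into six measures. Prosociality has three (Dictator Game, Social Value Orientation, Charitable Giving); forgiveness, empathy and perspective taking have one each. None is ranked, and no rule says how many must succeed.

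Under Analysis plan, Quantitative data, the decision rule is: "This study will consider a result with a p-value lower than 0.05 as statistically significant". It accompanies a series of repeated-measures MANOVAs comparing three conditions, both between groups and over time. Charitable Giving is compared separately because it is measured only at T2. Intention-to-treat and per-protocol analyses are both planned, and neither is called primary.

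Research question and hypotheses gives one directional between-group prediction: "We also hypothesise that these outcomes will be greater for participants in the heart-centred contemplations compared to those in the waitlist control condition". It makes no specific prediction against MBSR, although the key question names both comparators. The power analysis is for one test, "with an alpha value of 0.05, a desired power of β = 0.85".

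**The concern.** The protocol gives several primary measures equal standing and a threshold that applies to any one result. Nothing says which result carries the trial's conclusion. A single nominal p < 0.05 among the six could therefore be reported as a positive primary finding, and the error rate of such a claim is not 5%.

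The multivariate tests do not clearly limit this. The text does not say which outcomes enter which MANOVA, or that a univariate or pairwise result counts only after a significant multivariate one. Charitable Giving is outside the repeated-measures models. Perspective taking has three time points and the other repeated primary measures have two, so one joint model over T1 to T3 does not fit the schedule in Table 2. At stake is whether a positive primary claim can be taken at face value. That can be credibly repaired only before results are seen.

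**Working it through.** **Inputs from the protocol.** Six primary measures; threshold 0.05; three conditions, hence three possible pairwise contrasts; planned total 288 with 10% dropout; effect size 0.1; power 0.85; the power analysis "considering four groups with mixed method repeated measures at three timepoints".

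**Assumed, because the protocol does not give them.** Correlation between outcomes, varied from 0 to 0.7. Condition sizes of 144/72/72 (72 in each of four groups, the two spiritual groups pooled) or 96/96/96. For the power model, correlation 0.5 between time points and sphericity.

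**Step 1: reproduce the sample size.** For the within-between interaction of a repeated-measures ANOVA, the noncentrality is λ = f²·N·m/(1−ρ), with df (k−1)(m−1) and (N−k)(m−1). With f = 0.1, k = 4, m = 3, ρ = 0.5 and alpha 0.05, 85% power first occurs at N = 258, where λ = 0.01 × 258 × 3/0.5 = 15.48 on 6 and 508 df. Dropout: 258/0.9 = 287, or 288 in equal groups of 72. The protocol's figure is reproduced, for one test at 0.05. (It reproduces with 0.1 read as f. Read literally as f² = 0.1, N would be 29.)

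**Step 2: independent tests.** The chance of at least one false positive in n tests is 1 − 0.95ⁿ.
- n = 6: 1 − 0.95⁶ = 26.5%
- n = 2: 1 − 0.95² = 9.8%
- n = 3: 1 − 0.95³ = 14.3%

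**Step 3: correlated outcomes and shared arms.** Simulation of six normal outcomes with no true effects; ranges cover the two allocations.

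| Outcome correlation | One contrast, or one omnibus test, per measure | Spiritual v each comparator | All three pairs, no gate |
|---|---|---|---|
| 0 | 27% | 44–45% | 54% |
| 0.3 | 24–25% | 40–42% | 50% |
| 0.5 | 20–21% | 35–36% | 43–44% |
| 0.7 | 16–17% | 28–30% | 35–36% |

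**Step 4: the reading most favourable to the plan.** Suppose one joint RM-MANOVA covers the repeated primary measures and gates all follow-up, with Charitable Giving tested separately. That is two tests, at most about 9.8%, or three tests and 14.3% if perspective taking needs its own model. This protection holds only when no measure responds. If one measure truly responds and opens the gate, five true nulls tested at 0.05 give 1 − 0.95⁵ = 22.6% if independent.

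**Step 5: the price of correction.** Holm's first step is 0.05/6 = 0.0083. In the Step 1 model with 259 completers (288 × 0.9), power falls from 85% to 65%. Restoring 85% would need N = 360, or 400 with dropout.

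**The case against.** The strongest reply is that this is a condensed article. A statistical analysis plan may exist, and the grouping of outcomes, gating and post-hoc procedure are commonly left to it. A statement of alpha is conventional and does not rule out adjustment. That is fair as far as the missing detail goes. The point rests on what is written: six primary measures of equal rank, a flat threshold for any result, and a sample size computed for one test at 0.05. A later correction would alter that rule and the premise of the sample size.

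Three further objections stand and limit the point.
- A reader might infer that each measure is tested alone and that the MANOVA protects nothing. The protocol does not say so; a joint, gated test would bring the figure to about 10% to 14% when nothing works.
- A reader might infer a chance near 1 in 2. That needs ungated pairwise tests, whereas the plan describes a comparison among conditions. With three groups, pairwise follow-up only after a significant omnibus test keeps each measure near 5%, so the extra contrasts need not add error.
- A reader might infer that no contrast has priority. None is labelled primary, but spiritual versus waitlist is the only directional between-group hypothesis.

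The first hypothesis also lists the constructs jointly. If all had to succeed there would be no inflation, but the protocol states no such rule.

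**Conclusion.** The concern holds in a limited form. With the six measures tested separately on spiritual versus waitlist, the chance of at least one false-positive primary result is about 16% to 27%, roughly three to five times the nominal 5%. It is about 35% to 54% only under ungated testing of all three pairs, which the plan does not state. The reading kindest to the plan still gives about 10% to 14% under the global null.

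These figures rest on assumed outcome correlations of 0 to 0.7, on normal outcomes, and on no true effect (apart from the partial-null figure in the working). They leave out the within-group tests over time and the second analysis set, both of which add opportunities for a nominally significant result.

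**What to change.** Before analysis, add a dated paragraph that designates spiritual meditation versus waitlist at T2 as the confirmatory contrast and adopts one of two options of equal standing:

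1. Name one measure as primary at 0.05, with the other five as key secondary. The stated alpha is kept and there is no loss from adjustment. The price is that the other five no longer carry a primary claim, and the sponsor must choose which measure leads.
2. Keep all six as primary and apply Holm across them. The first-step threshold is 0.0083, and power for a single measure in the protocol's own model falls from 85% to about 65%. Restate that power figure rather than enlarge the trial. The model is the four-group, three-time-point interaction, so 65% indicates the size of the loss and is not the power of the T2 contrast itself.

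Under either option, label the MBSR contrasts, T3 results and secondary outcomes as exploratory. No data collection changes.
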